### Sample size

The sample size needs to be sufficient to provide reliable evidence about whether family functioning is sufficiently impacted by the Baby Triple P for Preterm infants intervention to improve the primary outcome of child behavioural and emotional problems. A clinically important difference in child behavioural and emotional problems is considered to be a standardised effect size of 0.33 on the ITSEA [49]. This is a conservative estimate of the expected effect size observed in past RCTs of Triple P [36]. With a type-1 (alpha) level of 0.05, and 80% power, a total of 140 per group are required for analysis. Based on our experience, the expected retention rate is > 85% so that 330 families (n = 165 in each group) will be recruited to allow for attrition. As babies of multiple births cannot be considered independent, the unit of randomisation is family (or delivery), and the total number of babies recruited will depend on the number of multiple births. A total of ~675 families of preterm infants born at <32 weeks who survive to term equivalent are admitted to RBWH and MMH combined over the proposed 3 year recruitment period. Allowing for the estimated retention rate of 50% of those eligible, the feasibility is high of recruitment of a sufficient sample of at least 330 of the eligible 338 families to be studied at 24 months C.A.

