### Study treatments

*Content of Baby Triple P for Preterm infants:*

*Hospital based content:*

4 × 2 hr group sessions structured in incremental anticipatory guidance style will guide parents to:Identify personal stressors and enhance coping skills (e.g. awareness of common ‘early parent traps’, enhancing social support, relaxation skills, coping strategies)Knowledge of effective partner support strategies (e.g. communication skills, awareness of common partner traps, maintaining relationship happiness, negotiating a fair division of labour). Note that single mothers will identify a significant other to use these strategies with at recruitment.Recognise their baby’s needs (e.g. feeding/sleep, emotional needs, attention needs)Modify environmental influences to facilitate the development of well-organized behaviourTeach baby new skills (e.g. engaging activities, giving attention, praise)Develop a positive relationship (e.g. promoting alert state, robust sleep, addressing emotional needs)Deal with infant behaviours (encouraging contentment, establishing limits, using diversion).Deal with crying (why, how much, settling strategies, what to do when crying persists).

*Community based content:*
4 × 30 min telephone consultations soon after transfer from hospital with the Baby Triple P for Preterm infants hospital facilitator to allow for tailoring of Baby Triple P for Preterm infants content to individual family needs.Ongoing receipt of Triple P tip-sheets plus telephone support as required. Directly linked to local Triple P services already available in the community where possible.Fortnightly text messages reiterating program content.

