## Measures

### Sample descriptors and prediction variables

*Family background questionnaire* (FBQ; assessed at baseline, post intervention, at 12 and 24 months C.A.) Assesses maternal and family factors, socio-economic status, education level and whether it was a planned pregnancy to determine impact on outcome.*Medical risk factors* (assessed at baseline) for outcome from the child’s case notes using the standardised Australian and New Zealand Neonatal network data definitions (e.g. GA, birth weight, disease severity, PIVH [50], PVL) [1].*The Gross Motor Function Classification system* (GMFCS; assessed at 24 months C.A.) is a valid and reliable way to classify the functional abilities of children with cerebral palsy and physical disability.*Social Support Scale* (SSS): will be assessed at baseline, 6 weeks post and 12 months C.A [40]: The SSS is a 4-item measure of the parent’s satisfaction with their social support network. The first two items referred to *formal support* (help that people get from professionals or organisations such as child health nurses or paediatricians) and asked participants to a) list the people they receive formal support from using initials and b) how satisfied they are with the extent of formal support they currently receive (from 1 = *Not at all satisfied* to 5 = *Completely satisfied*). The second two items referred to *informal support* (support that is not paid for and often provided by family, friends and neighbours) and asked participants to a) list the people they receive informal support from using initials and b) how satisfied they are with the extent of informal support they currently receive (from 1 = *Not at all satisfied* to 5 = *Completely satisfied*). Listing people participants receive support from was used as a prompt to think about their support network and these items were not used for data analysis.

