
*Child Cognition and Language:*
*The BSID III* [57] will be administered at 24 months C.A. to assess early cognitive development, language and motor abilities. It takes up to 1.5 hours to administer.*The CSBS DP Infant-Toddler Checklist* [58] will be completed by mothers during the ‘parent busy’ segment of the mother-toddler observation conducted at 24 months CA. For use with parents of children from 6 to 24 months of age, the ITC is a broader developmental screen that identifies children with developmental, in particular language and communication delays as well as children with an autism spectrum disorder (ASD). The ITC consists of 24 questions about early social communication behaviour (e.g. "Does your child let you know when he/she needs help or wants an object out of reach?"). Each item is rated on either a 3 or 4-point scale i.e. Not Yet (0), Sometimes [1], Often [2]. Sensitivity of the ITC for identifying developmental delays is 83%.*Maternal Infant Responsiveness Instrument* [59] (MIRI); will be assessed at 6 weeks and 12 months CA. The MIRI is a 22-item self-report questionnaire measuring maternal responsiveness to infant cues with high internal consistency (α = 0.87) [60] and face and content validity that has been established using advanced nurse practitioners and maternal child nursing experts [59].*Maternal Postnatal Attachment Scale*: (MPAS) will be assessed at 6 weeks and 12 months CA [61]. The MPAS is a 19-item self-report questionnaire measuring mother-to-infant attachment. It has high internal consistency (α = 0.78, 0.79 and 0.78) at four weeks, 4 months, and 8 months respectively, and construct validity that has been established with significant negative correlations with infant temperament and maternal negative affective states [61].*Parenting Scale* [62] (*PS)*: assessed at 24 months CA: The PS is a 30-item measure of 3 dysfunctional parenting styles: laxness (α = .83); over-reactivity (α = .82) and verbosity (α = .63). Reliability is strong (α = .84). Each item requires the parent to rate the likelihood of using a particular discipline strategy in response to common child misbehaviours using a 7-point Likert-type scale. Item scores are summed then averaged to give a total score ranging from 1 to 7. The PS is a valid and reliable tool, with good test–retest reliability (r = .84) and strong discriminant validity between parents of clinic/non-clinic children. The PS has been recommended as a tool for measuring parenting skill [62,63].*Parenting Scale* (PS-12 M): has been adapted for parents of children aged 12 to 18 months and will be assessed at 12 months CA [64]. A 21-item measure that has been adapted to match the language, behaviour and parent–child interactions appropriate for younger children 12–18 months of age. Each item requires the parent to rate the likelihood of using a particular discipline strategy in response to common challenging behaviours using a 7-point Likert-type scale. Item scores are summed to give a total score. Factor analysis revealed a one factor solution with good test reliability (r = .56, p = .01) and strong convergent validity (r = −.77, p = .006).*Maternal Self-Efficacy Scale* (MSES) [44]: will be assessed at 6 weeks post intervention, then at 12 and 24 months CA. The MSES is a 10-item measure of parents’ self-efficacy that has good internal consistency (α = 0.86) and a strong concurrent validity with the PSI Sense of Competency Scale [65]. At 24 months, an adaptation of this scale for toddlers will be used [44].*Brief Child Abuse Potential Inventory* [66] (BCAP): will be assessed at 24 months CA. The BCAP is a 33-item measure of the potential for child abuse with strong internal consistency (α = 0.89) and correlation (*r* =0.96).*Edinburgh Postnatal Depression Scale* [67] (EPDS): will be assessed at baseline, at 6 weeks post intervention then at 12 months CA. The EPDS is a 10-item screen for postpartum depression with good internal (α = 0.80) and test-retest (α = 0.77) reliability.*Depression, Anxiety and Stress Scale-21* [68] will be assessed at 24 months C.A. The DASS-21 is a 21 self-report item questionnaire reflecting the frequency or severity of the participant’s experiences with depression, anxiety and stress over the past week with high internal consistency (α = 0.83, 0.78 and 0.87 for depression, anxiety and stress respectively [69]. High convergent validity has been established between the DASS and other measures of similar constructs: DASS depression scale and the Beck Depression Inventory *(r* = .76), DASS anxiety scale and the Beck Anxiety Scale (*r =* .74*)* and DASS stress scale and the Positive and Negative Affect Schedule (*r* = .74) [70].*Relationship Quality Index (RQI* [69]; will be assessed at baseline, at 6 weeks post intervention then at 12 and 24 months CA [69]. The RQI is a 6-item questionnaire of relationship satisfaction with good internal consistency (α = .68-.86), reliability (α = .90) and discriminant validity. The scale consists of 5 specific items regarding relationship health and 1 global item reflecting global overall relationship satisfaction. A higher score corresponds to higher relationship satisfaction. The RQI has good internal consistency (α = .68-.86;) [69] and reliability (α = .90).*Frequency and Acceptability of Partner Behaviour* (FAPBI) [71]: will be assessed at baseline, at 6 weeks post intervention, then at 12 months CA. The FAPBI is a 19-item measure of the frequency and acceptability of positive and negative partner behaviours with strong internal consistency (α = .73-.85), correlation (*r* = .43-.58) with partner-reports and strong discriminant validity between couples seeking marital therapy and non-clinic couples.*Rapid KPI coding system* [72]: will be assessed at baseline, then at 6 weeks post treatment and 12 months C.A. The KPI will be used to code a video or audio recorded 10-min observation of couple interaction for parents in a relationship, discussing a topic of current conflict. Parents will be provided with a list of possible topics centring on baby care tasks or couple issues. Parents living within a 100 km radius of Brisbane will complete the task either in-home or at the hospital, video-recorded by a researcher. Couples who live beyond 100kms will receive an audio-recorder to complete the task independently, and will post this back using a reply paid envelope. Couple communication is scored in 30s intervals for conflict, validation and verbal affect. The KPI has good internal consistency (positive discussion: κ = .65, validation: κ = .58, invalidation κ = .69, conflict κ = .62, and negative nonverbal behaviour κ = .59 [72], is sensitive to change and has been used to measure changes in couple communication from couple’s therapy [72-74].*Parent Problem Checklist – Baby* (PPC-B): will be assessed at 6 weeks post intervention then at 12 months CA [75]. The PPC-B is a 16-item questionnaire which measures conflict between parents over child rearing. The PPC-Baby has demonstrated strong internal consistency (α = .70) and good test-retest reliability (*r* = .90) with a subset of clinic parents who completed the scale again after an 8-week interval [75].*Parenting and Family Adjustment Scale* [76]. (PAFAS): will be assessed at 24 months C.A. The PAFAS assesses parenting practices and parent and family adjustment. It consists of a 28-item Parenting Scale encompassing two domains including parenting practices (17 items) and parent–child relationship (11 items) and of a 12-item Family Adjustment scale encompassing three domains including parental emotional maladjustment (5 items), family relationships (4 items) and parental teamwork (3 items). Each item is rated on a 4-point scale from not true of me at all (0) to true of me very much [3]. This study will use only the three items from the parental teamwork domain which has good internal consistency (coefficient H = .85). The PAFAS has satisfactory construct and predictive validity [76].*Client Satisfaction Questionnaire* (CSQ): will be administered at 12 and 24 months C.A. for the intervention group only. The CSQ is a 10 item measure of the parent’s satisfaction with the parent training program. It is an adaptation of the Therapy Attitude Inventory (TAI) [77]. The TAI has established reliability, internal consistence and discriminant validity.

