
### Analyses

Analysis will follow standard principles for randomised controlled trials using 2-group comparisons performed using all subjects for whom outcome data are available, on an intention-to-treat basis. The experimental unit is a family. The effect of clustering for children in multiple births will be partitioned from the experimental error, which will be estimated from the between family variability. Up to 50% of eligible families may not consent or alternatively, be back-transferred to regional hospitals before an approach can be made, and a further 15% may be lost to follow-up at 2 years. Consequential threats to external and internal validity will be checked using baseline and descriptive information for eligible families. Imputation techniques will be used to avoid bias which may be a consequence of non-ignorable missing data during follow-up. All data analyses were performed using STATA 10.0 (Statacorp 2007).

The primary endpoint at 24 months C.A. is the child behavioural and emotional problems as measured on the ITSEA and the mother-toddler observation. This comparison will be between treatment groups using general linear models, with terms included for stratification and important confounding variables, such as the extent of brain injury and socio-demographic variables. Secondary analyses will use similar methods to compare the outcomes between groups for the additional outcomes (cognition, language etc.). For dichotomous outcomes, comparison will be by chi-square tests and multiple logistic regression. Where continuous data exhibit substantial skewness not overcome by transformation, non-parametric methods (Mann–Whitney *U* test) will be used for simple comparisons. Further analysis will be performed using latent growth modelling (LGM) [78,79] as it provides simultaneous analysis of time points and can incorporate latent measures corrected for measurement error [80]. The added-growth LGM used in evaluating the efficacy of Baby Triple P for Preterm infants tests the extent to which the intervention alters the trajectory of the target behaviour [79]. The models may incorporate main effects of time-independent and dependent covariates (e.g. control variables) on trajectories, as well as interactions of such measures with intervention effects [78,79]. The models express the expected change in dependent variables as a function of exposure to the intervention (e.g. Baby Triple P for preterm infants versus Control).

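### The supplementary growth models may control for post-randomisation variables that the programme aims to change, and the stated model for parent and couple outcomes omits the baseline scores already collected

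*Protocol article*

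**What the plan says.** The Analyses section describes two layers of modelling.

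- **Main comparison.** The 24-month primary endpoint is compared by general linear model: "This comparison will be between treatment groups using general linear models, with terms included for stratification and important confounding variables". Brain injury and socio-demographic variables are given as examples. Secondary outcomes are to be analysed by similar methods.
- **Further analysis.** Latent growth models are added and described as a means of evaluating efficacy. On their covariates: "The models may incorporate main effects of time-independent and dependent covariates (e.g. control variables) on trajectories". Interactions of such measures with the intervention effect are also allowed.

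Four other places bear on this.

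- *Sample descriptors and prediction variables* lists the Social Support Scale, which "will be assessed at baseline, 6 weeks post and 12 months C.A".
- *Study treatments* puts "enhancing social support, relaxation skills, coping strategies" among the content of the hospital group sessions.
- The secondary hypothesis H3 names parenting style, self-efficacy, parental mental health and relationship satisfaction as outcomes, and plans to test whether they mediate the effect on the child.
- The measures section gives baseline scores for EPDS, FAPBI and KPI (each also at 6 weeks and 12 months) and for the RQI, which "will be assessed at baseline, at 6 weeks post intervention then at 12 and 24 months CA". Under *Consent, randomisation, stratification*, the baseline assessment is completed before allocation.

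**The concern.** A covariate measured after allocation can itself be changed by the treatment. If such a variable enters an efficacy model as a control, the treatment coefficient no longer measures the effect of being offered the programme. It measures what is left once the pathway through that variable is removed. The same section promises an intention-to-treat analysis, and H3 treats some of these variables as pathways. The growth-model sentence does not keep the two roles apart, so which variables become controls could be settled after the data are seen.

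The second part concerns precision. For a parent or couple outcome measured before and after randomisation, the baseline score is usually the strongest single predictor of the later score. A model without it leaves that explained variance in the error term. It also lets a chance difference between groups at baseline, for example in depression or relationship quality, carry into the estimated effect.

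**Working it through.** **1. The plan's own figure.** The only power calculation is for ITSEA: the important difference is "considered to be a standardised effect size of 0.33 on the ITSEA", and "With a type-1 (alpha) level of 0.05, and 80% power, a total of 140 per group are required for analysis". Taking the test as two-sided (sidedness is not stated), n = 2(1.96 + 0.8416)²/d².

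- d = 0.33: 15.70/0.1089 = 144.1, so 145 per group.
- d = 1/3: 15.70/0.1111 = 141.3, so 142 per group.
- Power at 140 per group with d = 0.33: Φ(0.33 × √70 − 1.96) = Φ(0.80) = 78.8%.
- 140/0.85 = 164.7, so 165 recruited per group.

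The figure reproduces closely. It is not used further, because it belongs to the ITSEA comparison, which neither part of this point reaches.

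**2. Time-dependent controls.** Let T be allocation, M a post-randomisation variable and Y the outcome, with M = aT + u and Y = c′T + bM + e. The total (intention-to-treat) effect is c = c′ + ab. A model that includes M as a control estimates c′. If a share m of the effect runs through M, then c′ = (1 − m)c. For illustration only, m = 25%, 50% or 75% leaves 75%, 50% or 25% of the total effect. The documents give no value for m. If M and Y also share unmeasured causes, c′ is not estimated cleanly either.

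The repeatedly measured variables, set against their role in the protocol:

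| Variable | Measured | Role |
|---|---|---|
| Social support (SSS) | baseline, 6 weeks, 12 months | prediction variable; taught in the sessions |
| Parental mental health (EPDS) | baseline, 6 weeks, 12 months | H3 outcome and possible mediator |
| Relationship satisfaction (RQI) | baseline, 6 weeks, 12 and 24 months | H3 outcome and possible mediator |

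Nothing in the growth-model text excludes the later values of these as controls.

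**3. Own-baseline score.**

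| Outcome | Baseline | 6 weeks | 12 months | 24 months |
|---|---|---|---|---|
| EPDS | yes | yes | yes | no |
| FAPBI | yes | yes | yes | no |
| KPI | yes | yes | yes | no |
| RQI | yes | yes | yes | yes |
| ITSEA | no | no | yes | yes |
| Mother-toddler observation (FOS) | no | no | no | yes |
| BSID III | no | no | no | yes |

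Adjusting for a baseline score that has correlation r with the outcome multiplies residual variance by 1 − r². The equivalent gain in sample size is 1/(1 − r²). Here r is assumed, and is taken as the correlation remaining after the other model terms.

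| Assumed r | 1 − r² | Variance reduction | 1/(1 − r²) |
|---|---|---|---|
| 0.3 | 0.91 | 9% | 1.10 |
| 0.5 | 0.75 | 25% | 1.33 |
| 0.7 | 0.51 | 49% | 1.96 |

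These figures apply only to the first four rows of the outcome table.

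**The case against.** The strongest reply has three parts.

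- **The growth model is supplementary and its covariates are optional.** The model is introduced as further analysis, and the sentence says covariates may be included. The protocol nowhere says that social support, or any other programme target, will be a control. That link comes from reading separate sections together. Time-dependent terms are also legitimate in the mediation analysis that H3 announces. All of this stands. It makes the point one about an unrestricted permission, not a declared misuse.
- **The covariate list is open and a fuller plan may exist.** Brain injury and socio-demographics are only examples, and a condensed article commonly leaves the covariates for each outcome to the analysis plan. This weakens the baseline part: the protocol does not say that baseline scores will be left out. What remains is that the method as stated can be improved using data already collected.
- **A growth model that includes the baseline wave already uses the baseline score.** This is correct. The baseline part therefore concerns the general linear model comparisons.

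A reader might go further and infer that the primary ITSEA comparison will be diluted by mediator adjustment, with a calculable loss of power from the planned 140 per group. The documents do not support that. The primary general linear model names no time-dependent covariate, and no mediated share is given. A reader might also infer that H1 and H2 lose precision through a missing baseline term. They do not, because ITSEA, FOS and BSID III have no baseline score to adjust for.

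**Conclusion.** The point holds in two limited parts. First, the supplementary growth models used in evaluating efficacy may take post-randomisation control variables without restriction, although several repeatedly measured variables are programme targets or declared mediators. Used that way, the models would estimate a direct effect and not the intention-to-treat effect. The size of the distortion cannot be derived from the documents.

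Second, the stated general linear model does not name the own-baseline score for EPDS, RQI, FAPBI and KPI. If the score would otherwise be left out, an assumed correlation of 0.3 to 0.7 implies that including it would lower residual variance by 9% to 49%. The actual correlations are not given.

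The primary comparison and the planned sample size are not affected.

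**What to change.** Make three changes of wording in the Analyses section or the analysis plan.

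1. In every model that estimates the treatment effect, including the growth models, allow only covariates measured before randomisation. Take socio-demographic terms from the baseline questionnaire, since that questionnaire is repeated later.
2. Keep post-randomisation measures for the mediation analysis under H3, and report it separately from the efficacy estimates.
3. Name the own-baseline score as a covariate for EPDS, RQI, FAPBI and KPI at 6 weeks and 12 months, and for RQI also at 24 months, unless the growth model already includes the baseline wave.

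No new data and no change in sample size are needed. The one cost is that families with a missing baseline score need a simple imputation so that they stay in the analysis.
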